#### Acupoint injection

2.5.2

The patient took a suitable position, exposed the skin of abdomen, waist and leg and located Guanyuan, Zusanli, and Sanyinjiao. After local disinfection, a 10 mL syringe was used to connect the No. 7 needle, and the needle was punctured slowly at the vertical acupoints. After the patient felt the sensation of acid swelling and no blood return after aspiration. Inject the medicine and about 0.5 to 1 mL was injected into each point. The acupuncture depth was about 2 to 3 cm. Drug composition: Huang Qi injection (China Wuxi SFDA approval number: Z32021030). After the injection, lie prone and rest for 30 minutes to observe whether the patient felt uncomfortable. The injection procedure was performed by the same doctor with >5 years of acupoint injection experience.

The observation group was combined with acupoint injection on the basis of pelvic floor rehabilitation training, whereas the control group was simply given rehabilitation training.

### Evaluation criteria and judgment of curative effect

2.6

#### Measurement of the degree of pelvic organ prolapse

2.6.1

Refer to pelvic organ prolaps quantitation (POP international quantitative framework) for grading method,^[13]^ which is divided into 5 degrees: Degree 0 without prolapse. Degree I, the lowest point of prolapse is above the hymen >1 cm (<−1 cm). Degree II, the lowest point of prolapse is above or below the hymen 1 cm (>−1 ∼ <1 cm); Degree III, the farthest part of prolapse is located in the subhymen >1 cm, but less than the vaginal length (>1 cm); Degree IV, the lower genital tract is completely everted, and the lowest point of prolapse is at least equal to the length of the vagina.

#### Pelvic floor muscle strength measurement

2.6.2

PHENIXU4 neuromuscular stimulation therapy instrument was used to detect pelvic floor muscle strength of patients, including mean muscle strength (amplitude) and fatigue value (percentage reduction of muscle strength per second) of class I and II muscle fibers.^[14]^

#### Evaluation of the curative effect of urinary incontinence

2.6.3

Urinary incontinence will be assessed using the International Incontinence Consultation Questionnaire.^[15]^

#### Incidence of adverse reactions

2.6.4

Includes any treatment-related discomfort during treatment and follow-up.

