**Conclusions::**

This study will evaluate the efficacy and safety of acupoint injection combined with pelvic floor rehabilitation in the treatment of postpartum pelvic floor dysfunction, and provide reliable reference for the clinical application of this project.

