## Introdoction

1

Pelvic floor dysfunction (PFD) refers to a group of diseases caused by weak supporting tissue of the pelvic floor, including pelvic organ prolapse (POP), stress urinary incontinence, sexual dysfunction, and so on.^[1]^ In China, the incidence of PFD in women is as high as 58.7%, of which POP is the most common (48.73%), followed by stress urinary incontinence (8.7%).^[2]^ Although PFD is not like a malignant tumor endangering the lives of women, because of the special nature of PFD, patients often suffer from great psychological pressure,^[3]^ It has become 1 of the 5 most common chronic diseases affecting women's physical and mental health and quality of life.^[4]^

The pathogenesis of PFD is complex. Previous clinical studies have shown that pelvic floor muscle injury and pelvic floor connective tissue relaxation caused by various causes are its main pathogenesis.^[5]^ Pregnancy and delivery can lead to impaired pelvic floor muscle function, reduced pelvic floor muscle strength, and further cause urinary incontinence, pelvic organ prolapse, and other pelvic floor dysfunction diseases.^[6]^

Acupoint injection is a kind of alternative therapy based on Chinese meridian theory, which injects drugs into specific acupoints and achieves the purpose of treatment by stimulating acupoints.^[7]^ It is found that acupoint injection can improve the function of pelvic floor circulation, improve muscle strength and muscle tension, and accelerate nerve conduction.^[8]^ Pelvic floor rehabilitation training is a first-line conservative treatment for the prevention and treatment of pelvic floor disorders.^[9]^ By exercising the muscles, the patient can increase the muscle volume and raise the levator plate and genital hiatus, thus improving the support of pelvic organs.^[10]^ At present, there is a lack of clinical research on acupoint injection combined with pelvic floor rehabilitation in the treatment of postpartum pelvic floor disorders. Therefore, we designed this randomized controlled trial to evaluate the efficacy and safety of acupoint injection combined with pelvic floor rehabilitation in the treatment of postpartum female pelvic floor disorders.

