### Randomization and blinding

2.4

In this study, patients meeting the research criteria were included through pre-hospital recruitment and inpatient screening. The random number generator in Microsoft Excel was used to randomly divide the patients into the observation group and the control group according to the proportion of 1:1. The clinical research coordinator entered participant information on the tablet and was given a random number. The research assistant got the allocation of participants from the computer. Throughout the study, the research assistant was responsible for screening, recruiting participants, and assigning random numbers to participants who had been included. Outcome evaluator was responsible for the evaluation of the scale. Given the practical nature of acupoint injection, participants and practitioners might be aware of random assignment. However, the evaluators of the research results, the statisticians of data statistics and analysis did not know about the distribution.

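### The safety outcome counts only discomfort attributed to treatment, which leaves the between-group comparison of adverse reactions open to attribution and ascertainment bias

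*Protocol article*

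**What the plan says.** Safety stands beside efficacy in the aim. The Introduction says the trial is to "evaluate the efficacy and safety of acupoint injection combined with pelvic floor rehabilitation in the treatment of postpartum female pelvic floor disorders", and the abstract's conclusions repeat it.

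The only definition of the safety outcome is in section 2.6.4 of the protocol article: "Includes any treatment-related discomfort during treatment and follow-up". It names no one who decides whether discomfort is related to treatment.

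On who knows the allocation, section 2.4 says three things:
- "participants and practitioners might be aware of random assignment";
- "the evaluators of the research results, the statisticians of data statistics and analysis did not know about the distribution";
- "The research assistant got the allocation of participants from the computer".

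The same section describes the evaluator's task in one line: "Outcome evaluator was responsible for the evaluation of the scale". Section 2.7 has one or two assistants collect all data, without saying whether the research assistant who holds the allocation is among them.

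On observation, section 2.5.2 tells women who have been injected to "lie prone and rest for 30 minutes to observe whether the patient felt uncomfortable". Only the observation group is injected. Both arms share twice-weekly training sessions and a weekly monitoring meeting for 12 weeks (section 2.5.1), assessments at baseline, week 4 and end of treatment, and a follow-up contact 8 weeks later (section 2.7). Section 2.8 assigns the Fisher exact test at P < .05 to categorical outcomes.

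**The concern.** A comparison of harms between randomised groups is protected by randomisation only if an event has the same chance of being counted in either group. A relatedness filter weakens that protection. In the observation group a symptom such as leg pain or dizziness can be put down to an injection, to the exercises or to neither. In the control group the injection is not available as an explanation. The same symptom can then pass the filter in one arm and fail it in the other, although nothing about its true frequency differs.

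Two further features act on the same count. The women who report discomfort, and the practitioners who hear of it, may know the group. And the document describes one occasion on which someone actively looks for discomfort, which only one group has.

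At stake is half of the stated aim. An excess of adverse reactions in the observation group could partly reflect attribution and closer observation. A similar count could hide harms that were not recognised as related.

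**Working it through.** **The plan's own figure.** No figure is given for the safety outcome. The only design figure is the sample size in section 2.3, which rests on muscle strength, and it reproduces. The difference is 21.01 − 19.37 = 1.64. The pooled SD is √((2.26² + 2.57²)/2) = 2.42. With one-sided α = 0.025, the noncentral t calculation gives power 0.798 at 35 per group and 0.809 at 36, hence 36, and 36/0.90 = 40. Only the 40 per group is used below.

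**The passages side by side.**

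| Step from symptom to counted event | Observation group | Control group |
|---|---|---|
| Treatments it could be attributed to | injection, rehabilitation | rehabilitation |
| Active look for discomfort that is described | 30 minutes after injection | none |
| Contacts common to both | sessions, weekly meetings, assessments, 8-week follow-up | the same |
| Knowledge of group among women and practitioners | possible | possible |
| Judge of relatedness | not named | not named |

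The first two rows differ by arm. The weekly meetings are an equal opportunity to report, but section 2.5.1 gives their content as the intensity, frequency and timing of training and does not mention adverse reactions.

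**Illustration of the mechanism, on assumed inputs.** The document gives no event rate and no probability that an event is noticed and attributed. Assume the same true rate r in both arms, 40 women per arm, and a probability of 0.90 that an event in the observation group is counted. Let c be that probability in the control group. The apparent excess is r × (0.90 − c). The rejection rate of the two-sided Fisher exact test at P < .05 was found by summing over all pairs of counts.

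| True rate r, both arms | c = 0.90: excess; rejects | c = 0.60: excess; rejects | c = 0.30: excess; rejects |
|---|---|---|---|
| 10% | 0 points; 1.4% | 3 points; 2.1% | 6 points; 5.4% |
| 20% | 0 points; 2.8% | 6 points; 6.9% | 12 points; 25.9% |
| 30% | 0 points; 2.9% | 9 points; 11.0% | 18 points; 47.1% |

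For example, at r = 20% and c = 0.60 the excess is 0.20 × 0.30 = 0.06. If the two counting probabilities are swapped, the same figures apply as an apparent deficit in the observation group. With unequal counting, false rejection runs from 2.1% to 47.1%. That range shows that the mechanism can be negligible or serious. It does not estimate what will happen in this trial.

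**The case against.** The strongest reply has four parts.

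**Blinded evaluators.** A reader might infer that relatedness is judged by someone who knows the group. The document does not say so. Section 2.4 says the outcome evaluators are unaware of the allocation, and adverse reactions are listed among the outcomes in section 2.6. Against this, the evaluator's described task is the scale, and no one is assigned to judge relatedness. An unblinded judgment is therefore possible but not stated. Even a blinded judge would receive reports from women and practitioners who may know the group, and a complaint at an injection site reveals it.

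**The post-injection rest.** A reader might infer that the comparison is certain to be biased against the injection. That is not supported. The rest is part of giving the injection, and discomfort seen then may be a real effect of the treatment that belongs in its safety record. Both arms also share frequent contacts and identical scheduled assessments. Closer observation could raise the observation group's count, while attribution by people who know the group could raise or lower it.

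**The wording.** The sentence says what the outcome includes. It does not say that other events go unrecorded, so one cannot conclude that unrelated events are lost. It remains true that the outcome as defined is made up of events judged related.

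**A condensed article.** Severity grades, seriousness, causality criteria and form fields may well be in a fuller protocol, and their absence is no fault here. The Discussion also concedes that strict double-blinding is not possible and may affect results. Both points stand. They do not answer this one, which concerns the outcome rule that the article does state.

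**Conclusion.** The point holds as a weakness in a stated rule. The outcome in section 2.6.4 depends on attribution to treatment, in a trial where one arm has an extra treatment to attribute to, reporting may come from people who know the group, no judge of relatedness is named, and the one described active check is confined to one arm. The between-group comparison of adverse reactions is therefore open to attribution and ascertainment bias.

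The direction is unknown. The size cannot be computed from the document, and the illustration rests wholly on assumed event rates and counting probabilities. The conclusion needs no assumption about who judges relatedness. It does assume that adverse reactions are to be compared between groups, which follows from the safety aim and from the listing of their incidence among the outcomes. It should be changed, because a definition that depends less on attribution is available at little cost.

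**What to change.** Redefine the outcome in section 2.6.4 as all adverse events, whatever their cause, during treatment and follow-up. Then:

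- ask about them in both arms with the same question, at contacts both arms already have: the weekly meetings, the scheduled assessments and the 8-week follow-up;
- make all-cause incidence the between-group comparison;
- keep judged relatedness as a secondary, descriptive field;
- report reactions seen during the post-injection rest separately, for the observation group, so that they are neither hidden nor mixed with events that had an equal chance of being found in both arms.

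The cost is a revised definition and a somewhat longer record. More minor, unrelated events will be captured, and these add some noise to the comparison. Treatment, visit schedule and sample size do not change. The change has to be in place before data are collected, because events that were never asked about cannot be reliably recovered afterwards.

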### Data collection and management

2.7

The data will be collected according to the evaluation criteria before the beginning of treatment, 4 weeks after the start of treatment and at the end of treatment. If patients drop out midway during the period, the reasons for withdrawal are recorded in detail, and the willingness of patients will be obtained if the data are used. Eight weeks after the end of treatment, each patient will be followed up by outpatient or telephone. The detailed records of the reasons for the loss of follow-up information cannot be collected. All data will be collected jointly by 1 or 2 assistants. Personal information of all patients will be collected, shared, and stored in a separate storeroom to protect the confidentiality before, during and after the test. Access to the database is limited to the researchers of this research group.

### Statistical analysis

2.8

We will use SPSS.18 (SPSS Inc, Chicago, IL) software to analyze the research data. Fisher exact test and the Mann–Whitney *U* test will be performed for comparison of both groups, for categorical variables and continuous variables, respectively. When *P* <.05, the difference is statistically significant.

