### Patients

2.2

Inclusion criteria were: age 22 to 45 years’ old; Primipara who is full-term and vaginal delivery; the examination was in accordance with the diagnostic criteria of PFD within 180 days after delivery; pelvic floor muscle ≤III level, POP international quantitative framework dividing ≤II degrees; participate voluntarily and sign the informed consent form.

Exclusion criteria were: patients with previous history of reproductive system surgery; patients with neurological diseases, respiratory dysfunction, and vital organ dysfunction; patients with PFD disease before pregnancy; patients with a history of severe uterine malformation; patients with allergy or contraindications to the medication used in this study.

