### Sample size

2.3

The calculation of sample size is based on mean and standard deviation of muscle strength scores of class I muscle fibers in pelvic floor muscles after treatment. According to the results of the pilot study, the experimental group was 19.37 ± 2.26, and the control group was 21.01 ± 2.57. Set α = 0.025, unilateral test, β = 0.20. According to the calculation of PASS15.0 software, 36 participants are needed in each group; the estimated withdrawal rate is 10%, so that 40 participants will be included in each group.

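### The planned group comparisons are unadjusted Mann-Whitney and Fisher tests, which are valid but leave unused the baseline values the trial collects and, if prolapse degree counts as categorical, its ordering

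*Protocol article*

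**What the plan says.** Section 2.8 (Statistical analysis) names two methods, Fisher's exact test and the Mann-Whitney U test, and allots them by variable type: "test will be performed for comparison of both groups, for categorical variables and continuous variables, respectively". Significance is declared at P < .05. The section names no covariate, change score or model, and gives no separate rule for ordinal variables.

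Section 2.7 (Data collection and management) provides for baseline measurement: "The data will be collected according to the evaluation criteria before the beginning of treatment". Measurements follow at 4 weeks and at the end of treatment.

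Section 2.6.1 grades pelvic organ prolapse on a scale "which is divided into 5 degrees", running in order from 0 to IV. Under section 2.2, women enter at degree II or lower.

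Section 2.3 (Sample size) rests on post-treatment strength of class I muscle fibres: "the experimental group was 19.37 ± 2.26, and the control group was 21.01 ± 2.57", with "Set α = 0.025, unilateral test, β = 0.20". It arrives at 36 per group, raised to 40 for 10% withdrawal. It does not name the test used.

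**The concern.** A woman's muscle strength before treatment probably predicts part of her strength afterwards. A two-sample test on the post-treatment value leaves that predictable part in the error term. An analysis that conditions on baseline removes it and also corrects the estimate for whatever baseline difference chance produces. Section 2.4 describes simple 1:1 allocation and mentions no stratification, so the described design does not limit such a difference either.

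Section 2.8 offers two classes of variable, categorical and continuous. A five-grade prolapse scale reads most naturally as categorical, which would send it to Fisher's exact test. That test gives the same P value however the degrees are ordered, so a consistent shift towards lower degrees counts for no more than a scattered difference.

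At stake are the precision of the treatment comparison and the power on prolapse degree in a trial of 40 women per group.

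**Working it through.** **Inputs from section 2.3.** Means 19.37 and 21.01, SDs 2.26 and 2.57, one-sided α = 0.025 (equivalent here to two-sided 0.05), power 0.80. Only the size of the difference matters for this check.

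- Difference: 21.01 − 19.37 = 1.64.
- Pooled SD: √[(2.26² + 2.57²)/2] = 2.420.
- Standardised difference: 1.64/2.420 = 0.678.

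**Step 1: the plan's own figure.** For a two-sample t test with n per group, the noncentrality is 1.64/(2.420 × √(2/n)) with 2n − 2 degrees of freedom. At n = 35 the power is 0.798. At n = 36 the noncentrality is 2.875 and the power is 0.809. So 36 is the smallest sufficient size, and 36/(1 − 0.10) = 40. Both stated figures reproduce.

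**Step 2: adjusting for baseline.** With correlation ρ between baseline and outcome, ANCOVA leaves residual SD 2.420 × √(1 − ρ²) and uses 2n − 3 = 69 degrees of freedom. The article gives no correlation, so ρ is an assumption and a range is shown.

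| ρ (assumed) | 1 − ρ² | Residual SD | Noncentrality | Power at 36 per group |
|---|---|---|---|---|
| 0 | 1.00 | 2.420 | 2.875 | 0.809 |
| 0.3 | 0.91 | 2.309 | 3.014 | 0.844 |
| 0.5 | 0.75 | 2.096 | 3.320 | 0.905 |
| 0.7 | 0.51 | 1.728 | 4.026 | 0.978 |

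The table ignores the small loss from chance baseline imbalance. Multiplying the variance by 1 + 1/(2n − 4) = 1 + 1/68 to allow for it gives 0.804, 0.839, 0.901 and 0.976. Even if baseline predicted nothing, adjustment would cost at most about half a point.

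**Step 3: size of a chance imbalance.** With 36 per group, the baseline difference between groups has standard error √(2/36) = 0.236 SD. Assume ρ = 0.5 and a baseline SD equal to the outcome SD. An imbalance of 1.96 standard errors then moves the unadjusted difference by 1.96 × 0.236 × 0.5 × 2.420 = 0.56, or 0.56/1.64 = 34% of the planned difference. The test's error rate already allows for this, but the unadjusted estimate carries it.

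**Step 4: the Mann-Whitney test itself.** Simulation with 100,000 trials at the planning values and normal data gives power 0.786 at 36 per group and 0.828 at 40. The asymptotic efficiency 3/π gives 0.791 at 36. For other shapes at 36 per group, power is 0.836 (logistic), 0.871 (t with 5 df) and 0.748 (uniform).

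**Step 5: prolapse degree.** The article gives no distribution, so these are illustrations over degrees 0/I/II at 36 per group, two-sided 0.05, 3,000 simulated trials each.

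| Assumed distributions | Fisher exact | Rank test |
|---|---|---|
| 50/35/15% vs 25/40/35% | 0.574 | 0.683 |
| 40/40/20% vs 20/40/40% | 0.478 | 0.595 |

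Two further settings, with control at 20/50/30%, give 41% against 53% for a common odds ratio of 2.5, and 56% against 68% for an odds ratio of 3. The loss is about 11 to 12 points each time.

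**The case against.** **The tests are valid.** Under randomisation both keep their type I error without adjustment, and chance imbalance is not bias. This stands. What remains is efficiency, and its size depends on a correlation that the article does not state.

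**The article is condensed.** Covariates, effect estimates and confidence intervals are often left to a fuller protocol or SAP. That stands for anything merely absent, and the missing confidence interval is not a fault in itself. But section 2.8 does name the methods of comparison, and those have no place for a covariate. A SAP with ANCOVA as main analysis would depart from this text.

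**A change score would fit the wording.** Section 2.8 does not say which value is compared, and Mann-Whitney on change from baseline is possible. With equal variances, however, the variance of a change relative to the post-treatment value is 2(1 − ρ): 1.4, 1.0 and 0.6 for ρ = 0.3, 0.5 and 0.7. ANCOVA has 0.91, 0.75 and 0.51, so it is more precise throughout this range.

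**Prolapse degree is not assigned to Fisher's test.** Correct: section 2.8 assigns no individual outcome, and a rank test may be intended. This part is therefore conditional. No power was promised for prolapse either, since section 2.3 sizes the trial on muscle strength.

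**Two stronger readings are tempting.** A reader might infer that Mann-Whitney fails to deliver the planned 80% power. The documents do not support that as a material error. The shortfall at 36 per group is about 1 point under normal data, it reverses with heavier tails, and power is about 83% if all 40 enrolled are analysed. Section 2.3 also leaves the sizing test unnamed: the normal-approximation size of 34.18, divided by 3/π, is 35.8, so 36 could already allow for a rank test. A reader might also infer that natural recovery differs greatly across the entry window. Section 2.2 says only "the examination was in accordance with the diagnostic criteria of PFD within 180 days after delivery" and offers no recovery data.

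**Conclusion.** The point holds as a matter of efficiency. The stated comparisons do not use baseline although it is measured, and the better method costs almost nothing. At 36 per group and the planning values, power rises from about 81% for an unadjusted t test to about 84%, 91% or 98% for assumed correlations of 0.3, 0.5 or 0.7. The gain disappears only if baseline is close to uninformative.

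The prolapse part holds only if the degree is treated as categorical. The loss of about 11 to 12 points rests on assumed distributions.

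The planned tests are neither biased nor invalid, and the sample size is not shown to be inadequate for them. A change to section 2.8 is advisable, not a condition for a sound trial.

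**What to change.** Reword section 2.8, before unblinded data are seen, along these lines:

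- **Continuous outcomes:** the main analysis is ANCOVA of the post-treatment value on group and the baseline value of the same outcome, reporting the adjusted mean difference with its 95% CI. Mann-Whitney is kept as a sensitivity analysis.
- **Prolapse degree:** a proportional-odds model adjusted for baseline degree or, more simply, a rank test. State which.
- **Adverse-reaction incidence:** Fisher's exact test, as now.

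Days since delivery is at most an optional extra covariate. It must be known to apply the 180-day criterion, but section 2.7 does not list it among the collected data.

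The cost is a change of wording and a little more analysis work. The outcome baselines are already collected, and SPSS 18 can fit these models. The price is reliance on model assumptions (linearity and roughly normal residuals for ANCOVA, a common odds ratio for the ordinal model). The Mann-Whitney sensitivity analysis covers this for the continuous outcomes, and the rank test is the fallback for prolapse degree.

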**Methods::**

This is a prospective randomized controlled trial to study the efficacy and safety of acupoints injection combined with pelvic floor rehabilitation. And it is approved by the Ethics Committee of Clinical Research of our hospital. Patients were randomly divided into observation group (acupoint injection combined with pelvic floor rehabilitation group) or control group (pelvic floor rehabilitation group alone). The patients were followed up for 8 weeks after 12 weeks of treatment. The observation indexes included: pelvic organ prolapse degree, pelvic floor muscle strength, urinary incontinence score, adverse reactions, among others. Data were analyzed using the statistical software package SPSS version 18.0.

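### No primary outcome or time point is named, and every comparison is judged at P<.05, although the trial is sized on one outcome only

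*Protocol article*

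**What the plan says.** - **Outcomes.** The abstract (Methods) gives an open, unranked list: "pelvic organ prolapse degree, pelvic floor muscle strength, urinary incontinence score, adverse reactions, among others". Sections 2.6.1 to 2.6.4 set out the same items side by side. Section 2.6.2 alone holds four variables: strength and fatigue, each for class I and class II fibres.
- **Time points.** Section 2.7 collects the evaluation criteria before treatment, at week 4 and at end of treatment. Treatment lasts 12 weeks. A contact 8 weeks later may be by clinic visit or telephone, and its outcomes are not stated.
- **Sizing.** Section 2.3 rests on the "mean and standard deviation of muscle strength scores of class I muscle fibers in pelvic floor muscles after treatment", with "Set α = 0.025, unilateral test, β = 0.20". It never calls this outcome primary.
- **Decision rule.** Section 2.8 names Fisher's exact test and the Mann–Whitney test, then says that, for P below .05, "the difference is statistically significant". It gives no order of outcomes and does not say whether P is one- or two-sided.

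**The concern.** A trial sized for one test should say that this test decides it. Here the outcome behind the sample size appears only in section 2.3, and the analysis section does not refer to it. Even there, the words on timing are not tied to a visit. As written, a significant result on fatigue of class II fibres at week 4 has the same standing as one on class I strength at week 12. A reader of the results could not tell a confirmed effect from the best of many comparisons. The deciding test should also be fixed early because, according to section 2.4, participants and practitioners may know the allocation.

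**Working it through.** **1. Reproduce the sample size.** Inputs from section 2.3: "the experimental group was 19.37 ± 2.26, and the control group was 21.01 ± 2.57"; one-sided α = 0.025; power 80%.

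- Difference: 21.01 − 19.37 = 1.64.
- Pooled SD: √[(2.26² + 2.57²)/2] = 2.420.
- Standardised difference: 1.64/2.420 = 0.678.
- Normal approximation: n = 2(1.960 + 0.842)²/0.678² = 34.2, so 35 per group.
- Two-sample t-test (noncentral t): power is 79.8% at n = 35 and 80.9% at n = 36, so 36 per group. This matches "36 participants are needed in each group".
- Dropout: 36/(1 − 0.10) = 40, as stated.

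**2. Compare the two alpha levels.** One-sided 0.025 and two-sided 0.05 share the critical value 1.96. A two-sided 0.05 therefore gives the same 36 per group.

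**3. Count the tests.** Efficacy measures in section 2.6: prolapse degree (1), class I and II strength (2), class I and II fatigue (2), incontinence questionnaire (1). That is six. Post-baseline visits at which section 2.7 collects them: week 4 and end of treatment. Tests: 6 × 2 = 12.

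**4. Chance of at least one false positive with no treatment effect.**

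- Independent tests, either direction: 1 − 0.95¹² = 46.0%.
- Independent tests, observation group favoured: 1 − 0.975¹² = 26.2%.
- Correlated tests: each statistic is Z = √r·U + √(1 − r)·e, with U common to all 12 tests and r the same for every pair. A false positive is any |Z| > 1.96, or any Z > 1.96 when only one direction counts.

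| Correlation r (assumed) | 12 tests, either direction | 12 tests, favouring observation group | 6 tests (one visit), either direction |
|---|---|---|---|
| 0 | 46.0% | 26.2% | 26.5% |
| 0.5 | 31.9% | 16.0% | 20.7% |
| 0.7 | 23.2% | 11.6% | 16.4% |
| One test alone | 5% | 2.5% | 5% |

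At 12 tests the either-direction error is 4.6 to 9.2 times 5% (23.2/5 to 46.0/5). The favourable-direction error is 4.6 to 10.5 times 2.5% (11.6/2.5 to 26.2/2.5).

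**5. Direction.** The pilot means in section 2.3 put the experimental group below control by 1.64. Section 2.6.2 defines strength as an amplitude. The article does not say whether a higher or lower value is better, or whether this amplitude is the score used for sizing.

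**The case against.** The best defence is that section 2.3 already identifies the main outcome by sizing on it. On this view section 2.8 merely defines significance and does not say when the treatment is declared effective, and the handling of secondary outcomes may sit in a fuller plan that is not shown. Part of this stands. A missing multiplicity rule for secondary outcomes is not a fault by itself in a condensed article, and class I strength is clearly the natural candidate for primary. But the article states its only decision rule, and that rule treats all comparisons alike. It gives the sizing in full without saying that this outcome decides the trial, or at which visit.

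The independence figures are an upper limit, and this objection stands too. Strength, fatigue and repeated measures in the same women are unlikely to be independent, which is why the correlated figures are given.

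Three stronger readings are tempting, and the article does not support them:

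- **The alpha levels conflict.** A reader might set the one-sided 0.025 in section 2.3 against the .05 in section 2.8. They conflict only if the latter is one-sided, and nothing in section 2.8 says so.
- **There are 18 tests.** This counts all six measures again at the 8-week follow-up. Section 2.7 allows that contact by telephone, which cannot yield device-measured strength or a prolapse examination, and it lists no outcomes for it.
- **The chance of a false claim of benefit is 46%.** That figure also counts results favouring control. The figure for benefit is 26% or less.

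**Conclusion.** The point holds. The article leaves the deciding outcome and visit unnamed and applies one threshold to all comparisons. Over 12 tests the false-positive chance is 46%, 32% or 23% (independent, r = 0.5, r = 0.7). For errors favouring the observation group it is about 26%, 16% or 12%, against 2.5%.

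These figures assume no effect on any measure, an equal correlation between all tests, and each test run exactly at its nominal level. The correlations are assumptions, since the article gives none. Fisher's exact test is conservative, so the true figures would be somewhat lower where it is used. Even one visit with six measures gives 16% to 26% in either direction over the same range.

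The sample size is not in question here: 36 and 40 per group are reproduced. On alpha, the only gap is that section 2.8 does not state that P is two-sided.

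**What to change.** 1. State in sections 2.6 and 2.8 that the single primary outcome is class I muscle strength at end of treatment (week 12), tested two-sided at 0.05, and that efficacy is claimed only on that test. This is equivalent to the one-sided 0.025 used for sizing, so the sample size does not change.
2. Call all other measures and time points secondary. Report them as estimates with 95% confidence intervals, or control them with Holm's procedure if claims on them are wanted.
3. State which direction of class I strength is favourable, and reconcile this with the pilot means in section 2.3 (19.37 in the experimental group, 21.01 in control).

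The cost is wording only. The downside is that secondary results cannot carry a claim of efficacy on their own.
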